### Criteria for discontinuing or modifying allocated interventions {11b}

Each patient can decide to stop participation in the trial at any given point in time without any further explanations. A distinction is made here as to whether patients wish to withdraw from the intervention, the assessments or the consent to the transfer of health insurance data. If patients only wish to withdraw from the intervention and the assessments, the health insurance data used to determine the primary outcome can still be collected. The three home visits of the case manager should ideally take place until the end of the following week after discharge from the index hospital stay and subsequently 42 days (+ 5 working days) and 180 days (+ 10 working days) after the initial discharge. In case of unforeseen events (unplanned hospital admissions), the visits will be rescheduled to the next possible date.

### Strategies to improve adherence to interventions {11c}

Adherence to the intervention is crucial and several procedures have been implemented to ensure it. During the time in the hospital, the case manager educates the patient (and/or his caretakers) about his/her chronic conditions and the self-management of their chronic conditions. Additionally, he/she trains the patient in the use of the “smart assistant.” Furthermore, the physiotherapist teaches the patients individual exercises which they can perform independently or with the help of the “smart assistant” at home. This facilitates that the patients (and his/her caretakers) understand the personal benefits of the intervention. The patient is provided with an individualized home exercise plan and it is automatically recorded whether and how long the patient watches the videos. Furthermore, participation in the outpatient physiotherapeutic treatments is documented on the tablet by the physiotherapist. In case of insufficient use of the videos or participation in physiotherapeutic treatments, the case manager can discuss possible problems with the exercises and motivate patients to conduct them. Further measures are not implemented because this trial aims at assessing the effectiveness of eliPfad to provide reliable evidence to decide on whether to include it in standard care for patients. Any additional, trial-specific incentives for patients in the intervention group would flaw the effects and bias the overall results.

### Relevant concomitant care permitted or prohibited during the trial {11d}

The only restriction for patients regarding concomitant care is the use of rehabilitation measures within the intervention period of eliPfad in the ambulatory setting. Patients who clearly state that they want to participate in rehabilitation measures before the 42nd day after discharge are not eligible for eliPfad (see “Eligibility criteria”). The reason is that eliPfad aims at reducing the number of rehabilitation measures because participating in eliPfad is considered to be a rehabilitation measure itself.

### Provisions for post-trial care {30}

Patients in the intervention group will be regularly treated by their GP in the same way as the control group after the final assessment by the case manager. No further interventions after the 6 weeks in the ambulatory setting are planned.

### Outcomes {12}

#### Time points, data collection, and outcomes

Four time points (T) are defined which are accompanied by timely scheduled assessments (A). All assessments are carried out by members of the study team in person to ensure the completeness of the data. Pretests of the single questionnaires and the entire data collection assessment were conducted to test duration and feasibility for the patient population. Depending on the visit, these assessments are carried out either in hospital or at the patient’s home:T0/A0: Baseline, immediately after randomization and up to 2 working days after admission to the internal ward (in the hospital).T1: Discharge day from the index hospital stay. A1 can be performed up to 3 days before scheduled discharge (in the hospital) or up to 3 days after T1 (in the patient’s home).T2: End of the intervention phase, 42 days after T1. A2 can be performed up to 5 working days after T2 (in the patient’s home); if A2 cannot take place in this period (hospital admissions, etc.), A2 can still be collected on day 60 at the most, counted from discharge from the index hospitalization.T3: 180 days after T1. A3 can be performed up to 10 working days after T3 (in the patient’s home).

The primary outcome is the number of unplanned rehospitalizations over 180 days after the end of the index hospital stay. Unplanned inpatient readmission is defined as the admission of a previously discharged patient due to unplanned events or deterioration of health that can no longer be treated in the outpatient setting. The rehospitalization frequencies are determined using collaborating health insurance companies’ data. In addition, at A3, the patients are actively questioned by the case manager about possible hospital stays in the last 180 days.

The secondary outcomes are the variables required for the testing of the secondary hypotheses. The variables collected, when they are collected and the type of source are listed below:

The following data will be obtained by A2 at the latest:Duration of index hospital stayDuration of stays in intensive or intermediate care units during the index hospital stayDuration of stays in other departments within the index hospital stay, if these departments are not part of the local eliPfad teamTransfers to external hospitals including geriatric facilitiesLength of stays in external hospitals including geriatric facilities after the index hospital stayTransfers to rehabilitation facilitiesDuration of stays in rehabilitation facilities

The following data are collected using collaborating statutory health insurance companies’ data at A3:Frequency and type of use of services in outpatient and inpatient care, drug prescription, remedies, and aids between T1 and T3Number of rehabilitation services between T1 and T3Number of transfers to “acute” geriatric units between T1 and T3Length of stay in inpatient facilities (incl. hospitals and rehabilitation facilities)Death between T1 and T3The sum of costs based on the above-defined service areas of collaborating health insurance companies’ data between T1 and T3

The following data will be collected by questioning the participants (if necessary, the relatives, the treating physicians) at all survey points (A0–A3):Quality of life using EQ-5D-5LDepression using the Geriatric Depression Scale (GDL)Geriatric assessment using the Multidimensional Prognostic Index (MPI)Timed up and go Test (TUG)De Morton Mobility Index (DEMMI)Minimal Nutritional AssessmentHealth status using the Self-Rated Health QuestionnaireSelf-efficacy (General Self-Efficacy Short Scale, ASKU)Medication planHealth literacyThe personal treatment burden

The following data will be collected at the survey points A0, A2, and A3:Patient-centeredness of care using PACIC

The following data will be collected at A1, A2, and A3:

Questioning about personal therapy goals / self-management

The following data are recorded at A2 and A3:Actual number of drugs taken by the patient at home using photo documentation

The following laboratory values are documented as original values at A0 and A1:Determination of index diagnosis-specific blood parameters. The standard laboratory panel includes the following: blood count, glucose, sodium, potassium, chloride, phosphate, creatinine, urea, uric acid, ASAT, ALAT, gamma-GT, AP, bilirubin, total protein, albumin, lipase, LDH, CK, NT-proBNP, CRP, HbA1c24-h urine collection: volume, sodium, potassium, chloride, urea, uric acid, creatinine, albumin, total protein, and osmolality to determine dietary salt intake, urea appearance, renal function, concentration performance

The following laboratory values are documented as original values at A2 and A3:Determination of index diagnosis-specific blood parameters. The standard laboratory panel includes the following: blood count, sodium, potassium, creatinine, urea, uric acid, albumin, NT-proBNP, CRP, HbA1c24-h urine collection: volume, sodium, potassium, chloride, urea, uric acid, creatinine, albumin, total protein, and osmolality to determine dietary salt intake, urea appearance, renal function, concentration performance

All details and methods of data analysis will be documented in a statistical analysis plan (SAP). The SAP shall be finalized before database closure and will be approved by the two principal investigators and representatives of the evaluating statistics departments.

Data of process evaluation will be collected across the implementation of the intervention:Enabling and hindering factors from the perspective of the patients or their relatives, physicians, case managers, and study nurses in the implementation of eliPfad using individual interviews 3 months after the start of the study and continuously until the end of intervention.Examination of the acceptance of the intervention by patients or their relatives, physicians, case managers, and study nurses.Analysis of the quality of the intervention implementation.Survey of implementation hurdles in case of a national rollout through a nationwide online survey of general practitioners and specialists in private practice; this information will be collected using a website developed specifically for this purpose.

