## Trial design {8}

eliPfad is a pragmatic, randomized, controlled, open-label, multicenter trial with one intervention and one control group. The allocation ratio is 1:1. eliPfad is a superiority trial in which the superiority of the new model of care to the current standard of care is to be proven.

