**Clinical data collection**					
Evaluation of adverse events (AE)		X	X	X	X
Duration index hospital stay			X		
Duration stays in different wards			X		
Transfer to external hospitals			X		
Transfer to rehabilitation facilities			X		
MPI (geriatric assessment)	X		X	X	X
Health literacy		X	X	X	X
Quality of life/depression/health status/self-efficacy		X	X	X	X
Medication plan		X	X	X	X
Minimal Nutritional Assessment		X	X	X	X
Mobility tests		X	X	X	X
Patient orientation		X		X	X
Personal goals/self-management/personal therapy burden			X	X	X
Photo documentation drugs				X	X
Number of rehospitalizations				X	X
Health economic evaluation					X
Utilization of rehabilitation services					X
Length of stay in inpatient facilities					X
Death					X

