### Implementation {16c}

Potentially eligible patients are screened. This verifies that patients meet the inclusion and none of the exclusion criteria. This is performed by the study physician and study nurse. If all criteria are met, the study physician will inform the patient. Once the patient has given informed consent to participate in the study, their data is entered into the eCRF (hosted by secuTrial®). Subsequently, secuTrial® also carries out the randomization, and the study team is directly informed in which group the patient will participate in eliPfad.

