## Assignment of interventions: blinding

### Who will be blinded {17a}

Blinding of the participants is impossible given the kind of intervention of this trial. Assessors will not be blinded either, because patients in the intervention group will be in possession of the tablet and the medical devices. During the hospital stay, these items will be in close proximity of the patient and difficult to hide. At A2 it is the assessor’s task to take these items back to the study center after the assessment. Therefore, they need to know which patient is in which group. However, observer bias is not estimated to be a big problem, because all questionnaires are either filled in by the patient directly or require answers that need no interpretation by the assessor such as number of drugs prescribed or weight loss. Nevertheless, to minimize observer bias, all assessors are specially trained. All evaluators will be blinded.

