### Procedure for unblinding if needed {17b}

The design is open label with only outcome assessors being blinded so unblinding will not occur.

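### Baseline questionnaires and mobility tests are taken after open-label randomisation, so they can reflect the allocation, and the text and Table 1 disagree on whether treatment burden is measured at A0

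*Protocol article*

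**What the plan says.** **Order of events.** The Outcomes section defines the first time point as "T0/A0: Baseline, immediately after randomization and up to 2 working days after admission to the internal ward". Under Implementation {16c}, once secuTrial has randomised, "the study team is directly informed in which group the patient will participate in eliPfad". The Outcomes section also has study-team members carry out every assessment in person.

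**Blinding.** Trial design {8} states that "eliPfad is a pragmatic, randomized, controlled, open-label, multicenter trial with one intervention and one control group". Section {17a} adds "Blinding of the participants is impossible given the kind of intervention of this trial" and "Assessors will not be blinded either, because patients in the intervention group will be in possession of the tablet and the medical devices". Section {17b} then says "The design is open label with only outcome assessors being blinded so unblinding will not occur", which conflicts with {17a}.

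**Content of A0.** One list in the Outcomes section is introduced by "The following data will be collected by questioning the participants (if necessary, the relatives, the treating physicians) at all survey points (A0–A3". It contains EQ-5D-5L, the depression scale, MPI, TUG, DEMMI, the nutritional assessment, self-rated health, ASKU, medication plan, health literacy and, last, treatment burden. PACIC is listed for A0, A2 and A3. Therapy goals and self-management are listed separately, for A1 to A3.

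**Table 1.** The row "Personal goals/self-management/personal therapy burden" has marks at T1/A1, T2/A2 and T3/A3 only. Its Enrolment and T0/A0 cells are empty.

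**Analysis.** The statistical methods section {20a} assigns questionnaire scales to linear mixed models with repeated measurements and leaves details to the SAP.

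**The concern.** A baseline value can be adjusted for safely because allocation cannot have influenced it. Here the order of events removes that guarantee for measures that depend on how the patient feels, answers or performs. A patient who has just learned the arm may rate quality of life, mood, self-efficacy or patient-centredness differently, and effort in a mobility test may change too. An A0 difference caused in this way would carry into any contrast that subtracts A0 or adjusts for it. No analysis plan can recover a clean pre-allocation value afterwards.

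The article itself expects patients to react to open allocation. Its Discussion anticipates extra dropout among controls who no longer wish to take part. That concerns retention rather than scores, but it makes a reaction at A0 plausible.

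Treatment burden matters because it is a named secondary outcome and, in the abstract's discussion, one of the conditions for introducing eliPfad as standard care. If Table 1 is followed, its first value comes at A1, around discharge, although the hospital part of the intervention starts at enrolment. There would then be no pre-intervention value.

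**Working it through.** No figure in the article bears on this point, so there is none to reproduce. The check is a comparison of sections, followed by an illustration under stated assumptions.

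**1. Can A0 be influenced by allocation?**
- A0 follows randomisation (Outcomes {12}).
- The study team knows the arm at that moment ({16c}) and performs the assessment in person (Outcomes {12}).
- Assessors are unblinded and patients cannot be blinded ({17a}).
- The blinding statement in {17b} does not rescue A0. {17a} speaks expressly of the people who carry out the assessments and gives the reason they are unblinded.

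So the values can reflect allocation. The article does not state when the patient is told the arm.

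**2. What is not exposed?**
- The primary outcome comes from health-insurance data and does not depend on patient cooperation ({18a}, {18b}).
- The screening MPI is needed for eligibility (threshold 0.34) and so precedes randomisation. Table 1 accordingly puts it under Enrolment.

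**3. Does treatment burden have an A0 value?**

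| Source | A0 | A1 | A2 | A3 |
|---|---|---|---|---|
| Outcomes text, treatment burden | yes | yes | yes | yes |
| Outcomes text, therapy goals / self-management | no | yes | yes | yes |
| Table 1, merged row for goals, self-management and burden | no | yes | yes | yes |

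The neighbouring Table 1 row for health literacy has four marks beginning at T0, so the empty T0 cell in the merged row appears genuine and not an effect of text extraction. The merged row seems to have taken the schedule that the text gives to goals and self-management.

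**4. How large could the effect be?** The article gives no questionnaire SD, no correlation between visits and no allocation effect at A0. Everything here is assumption. Let knowledge of the arm improve the intervention arm's A0 mean by δ (in SD units), with equal SDs at A0 and follow-up, correlation ρ between them, and no carry-over of δ to follow-up. Then:
- Contrast at follow-up that ignores A0: bias = 0.
- Change from A0: bias = −δ.
- A0-adjusted contrast: bias = −ρ × δ.

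| δ | ρ | A0-adjusted | Change from A0 |
|---|---|---|---|
| 0.1 | 0.3 | −0.03 | −0.1 |
| 0.1 | 0.5 | −0.05 | −0.1 |
| 0.1 | 0.7 | −0.07 | −0.1 |
| 0.2 | 0.3 | −0.06 | −0.2 |
| 0.2 | 0.5 | −0.10 | −0.2 |
| 0.2 | 0.7 | −0.14 | −0.2 |

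A simulation with 400,000 patients per setting agreed to within 0.005 SD. The negative sign means that an intervention-favouring shift at A0 shrinks a true benefit. A shift the other way would inflate it.

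**The case against.** Several stronger readings are tempting, and the article does not support them.

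- **A reader might infer that A0 enters the models as a baseline, so that all scale comparisons are biased.** The statistical methods section names only mixed models with repeated measurements. It specifies no A0 covariate, change score or target contrast, and the SAP is not shown. A comparison of arms at A2 or A3 that does not use A0 carries no bias from this source. This objection stands, and the concern is conditional on that choice.
- **A reader might infer that patients know their arm when they answer.** Only the study team is said to be told at once. This stands as a limit: the values can reflect allocation, but it is not shown that they do.
- **Section {17a} argues that observer bias is small**, because patients complete the questionnaires or the answers need no interpretation. That speaks to the assessor's influence on the answers. It does not deal with a patient who knows the arm, nor with performance tests such as TUG and DEMMI.
- **A reader might infer that a missing A0 value would invalidate the burden comparison.** It would not. Randomisation still supports a comparison at A2 or A3. What is lost is precision and the ability to describe change from before the intervention. The Table 1 conflict is largely editorial, but it has to be settled because it determines what is collected.
- **The likely direction is conservative** in a superiority trial if enthusiasm or disappointment favours the intervention arm at A0. That is fair, but understating a real benefit is still an error, and the direction is not guaranteed for every scale.

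**Conclusion.** The point holds in limited form. The order of randomisation and A0, together with open allocation, means that the A0 patient-reported scales and mobility tests cannot be treated as guaranteed pre-allocation values. Secondary analyses that condition on A0 or use change from it could be biased. The size cannot be derived from the article. The range of 0.03 to 0.2 SD above rests wholly on an assumed 0.1 to 0.2 SD shift and, for the adjusted contrast, assumed correlations of 0.3 to 0.7. It should not be quoted as an estimate.

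The contradiction on treatment burden at A0 is plain and needs no assumption. It leaves unclear whether this secondary outcome has a pre-intervention value.

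Nothing here touches the trial's main conclusion on readmissions.

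**What to change.** 1. For patients still to be enrolled, take the A0 questionnaires and mobility tests after consent and before randomisation in secuTrial, within the same window of two working days. Laboratory tests and the 24-h urine collection can stay after randomisation; moving them is unnecessary and could delay allocation. The MPI is already assessed before randomisation, which suggests the order is workable.
2. Correct Table 1 so that treatment burden has a mark at that A0, in line with the Outcomes text, and separate it from the goals and self-management row.
3. For patients already enrolled, add a sensitivity analysis of the subjective scales that compares arms at A2 and A3 without conditioning on A0.

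**Cost.** The SOP and eCRF order changes slightly, and the ethics committee must be notified under {25}. The trial will contain two kinds of baseline, so the order should be recorded for each patient. A few patients will be assessed and then not randomised. The article gives 08/31/2025 as the end of recruitment; if enrolment has closed, the table correction and the sensitivity analysis are what remain.

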#### Explanation

The number of rehospitalizations has been selected as the primary outcome because revolving door effects leading to rehospitalizations are responsible for the majority of costs in the treatment of the target population and a common problem in this patient population.

### Participant timeline {13}

The participant timeline is depicted in Table 1.

**Table 1 Tab1:** Participant timeline. The time points are explained in the main manuscript (see 12)

	**Study period**				
	Enrolment	Allocation	Intervention		Post-intervention
Time point/assessment		T0/A0	T1/A1	T2/A2	T3/A3
**Study participation**					
Eligibility screen	X				
Informed consent	X				
Allocation		X			
**Clinical data collection**					
Evaluation of adverse events (AE)		X	X	X	X
Duration index hospital stay			X		
Duration stays in different wards			X		
Transfer to external hospitals			X		
Transfer to rehabilitation facilities			X		
MPI (geriatric assessment)	X		X	X	X
Health literacy		X	X	X	X
Quality of life/depression/health status/self-efficacy		X	X	X	X
Medication plan		X	X	X	X
Minimal Nutritional Assessment		X	X	X	X
Mobility tests		X	X	X	X
Patient orientation		X		X	X
Personal goals/self-management/personal therapy burden			X	X	X
Photo documentation drugs				X	X
Number of rehospitalizations				X	X
Health economic evaluation					X
Utilization of rehabilitation services					X
Length of stay in inpatient facilities					X
Death					X
**Laboratory data collection**					
24-h collection urine		X	X	X	X
Clinical chemistry		X	X	X	X

### Sample size {14}

Based on literature data and own calculations using data from the collaborating health insurance companies, a relative reduction of the readmission rate of about 25.9% over 6 months after (initial) discharge is expected (see also Berntsen et al, admission rate of 1.89/year corresponding to 0.95 over 6 months) (19) with the following distribution of absolute numbers (#) of readmissions per patient: #0—35%, #1—40%, #2—20%, #3—5% (Ø 0.95). eliPfad will result in a compression of this distribution as listed below: #0—49.5%, #1—33.1%, #2—14.9%, #3—2.5% (Ø 0.704). The Wilcoxon rank sum test was used to calculate the number of cases; by stratification, a power gain is additionally expected. Accordingly, a total of 474 patients (237 per group) are needed to detect this distribution difference with a power of 90% with a two-sided type I error of 5% [40] (R: A Language and Environment for Statistical Computing, Vienna, Austria, package samplesize, call: n.wilcox.ord (power = 0.9, alpha = 0.05, *t* = 0.5, *p* = c(0.35, 0.40, 0.20, 0.05), *q* = c(0.495, 0.331, 0.149, 0.025))). To compensate for up to 50% loss-to-follow-up in the control group and 30% in the intervention group, 474 patients should be randomized to each of the two groups (total 948 = 474/0.5). In the scenario given above, for the evaluation of the primary outcome measure using Poisson regression, the power of at least 90% was confirmed by simulation.

